## Abstract

**Background:**

The risk of falling is significantly higher in people with chronic stroke and it is, therefore, important to design interventions to improve mobility and decrease falls risk. Minimum toe clearance (MTC) is the key gait cycle event for predicting tripping-falls because it occurs mid-swing during the walking cycle where forward velocity of the foot is maximum.

High forward velocity coupled with low MTC increases the probability of unanticipated foot-ground contacts. Training procedures to increase toe-ground clearance (MTC) have potential, therefore, as a falls-prevention intervention. The aim of this project is to determine whether augmented sensory information via real-time visual biofeedback during gait training can increase MTC.

**Methods:**

Participants will be aged > 18 years, have sustained a single stroke (ischemic or hemorrhagic) at least six months previously, able to walk 50 m independently, and capable of informed consent. Using a secure web-based application (REDCap), 150 participants will be randomly assigned to either no-feedback (Control) or feedback (Experimental) groups; all will receive 10 sessions of treadmill training for up to 10 min at a self-selected speed over 5–6 weeks. The intervention group will receive real-time, visual biofeedback of MTC during training and will be asked to modify their gait pattern to match a required “target” criterion. Biofeedback is continuous for the first six sessions then progressively reduced (faded) across the remaining four sessions. Control participants will walk on the treadmill without biofeedback. Gait assessments are conducted at baseline, immediately following the final training session and then during follow-up, at one, three, and six months. The primary outcome measure is MTC. Monthly falls calendars will also be collected for 12 months from enrolment.

**Discussion:**

The project will contribute to understanding how stroke-related changes to sensory and motor processes influence gait biomechanics and associated tripping risk. The research findings will guide our work in gait rehabilitation following stroke and may reduce falls rates. Treadmill training procedures incorporating continuous real-time feedback may need to be modified to accommodate stroke patients who have greater difficulties with treadmill walking.

**Trial registration:**

Australia New Zealand Clinical Trials Registry, ACTRN12617000250336. Registered on 17 February 2017.

## Background

Stroke affects > 60,000 Australians every year, with 50% unable to walk one week following the event [1]. Impaired walking impacts independence by reducing the ability to perform everyday activities and limiting community participation [2, 3]. Falls risk is significantly higher in people with chronic stroke [4] and approximately 50% of people living at home after a stroke will fall within 12 months [9], with up to half sustaining multiple falls. Furthermore, in community-dwelling people with stroke, up to 77% of falls occurred during walking. While there has been considerable research investigating falls risk management for older people generally, high-risk groups, such as those who have had a stroke, have not been extensively studied with respect to targeted falls prevention. Traditional exercise-based falls-prevention programs are useful for the general older adult community but are not effective in people with stroke. For example, Batchelor et al. found that a multifactorial intervention including a home-based balance and strength program did not reduce falls in people with stroke [10]. Another study confirmed that a group- and home-based exercise program incorporating balance and strength training did not reduce falls [11]. This suggests that alternative, targeted treatments to reduce falls risk in people with stroke are urgently needed.

Stroke adversely affects sensorimotor function and muscle strength, inhibiting the capacity to activate appropriate muscles and increasing the risk of contact between the foot and either the supporting surface or objects on it. Said et al. [15] found, for example, that stroke participants who had difficulty in stepping over small obstacles (4 cm high) had greater falls rates. The key gait variable for predicting tripping-falls is minimum toe clearance (MTC), an event mid-swing in the walking cycle [5–8]. Low MTC increases the probability of unanticipated foot-ground contacts [7]. Given that tripping directly results from unsuccessful toe clearance, previous research with both young and older populations has focused on toe trajectory control during walking [6–8, 12–14]. Training individuals to increase MTC, therefore, has potential as a falls-prevention intervention.

The aim of this project is to determine whether real-time biofeedback of toe clearance during gait training can significantly minimize tripping risk in people with stroke. We will test the efficacy of real-time biofeedback as an intervention to increase MTC using a randomized controlled trial (RCT) design incorporating both a training or “acquisition” phase with biofeedback. Retention tests will be conducted to confirm *learning*, as demonstrated by the longer-term or “relative permanence” of the targeted behavior.

The primary objective is to determine whether real-time biofeedback of MTC during gait training will significantly increase MTC in people with stroke. We will also determine whether changes in MTC achieved on a treadmill transfer to overground walking. It is hypothesized that, compared to no-biofeedback training, visual biofeedback of foot clearance parameters during gait training will significantly increase toe-ground clearance (MTC) and MTC during biofeedback training will be retained in the longer term. It is also hypothesized that increases in MTC demonstrated in treadmill training will transfer to overground walking, such that tripping-risk in people with stroke is significantly reduced.

## Methods/Design

This single-blinded parallel group RCT with 1:1 randomization will assess the effects of biofeedback on MTC following gait training. It will conform to CONSORT guidelines and has been registered on the Australian and New Zealand Clinical Trials Registry (ANZCTR): ACTRN12617000250336. Ethics approval for the study was obtained from Austin Health, Melbourne Health, and Victoria University Human Research Ethics Committees. Informed consent procedures include the provision that participants clearly understand that they are free to withdraw at any time without providing a reason. The study design flowchart is shown in Fig. 1.

**Fig. 1 Fig1:**
[figure not shown]
Study design flowchart

### Patient population

#### Eligibility criteria for participants

Participants will be aged > 18 years, have sustained a single stroke (ischemic or hemorrhagic) at least six months previously, able to walk 50 m independently with or without a single point stick, and capable of providing informed consent. Exclusion criteria are: (1) an ankle foot orthosis; (2) neurological, orthopedic, cardiac, respiratory, or other medical conditions in addition to stroke that impact their ability to walk on a treadmill; (3) body mass > 158 kg (due to the weight limit of the harness); and (4) visual problems or severe visual-spatial neglect. Participants will not be receiving physiotherapy for their walking or lower limbs while enrolled in the study.

#### Participant recruitment study settings

Recruitment sites include Heidelberg Repatriation Hospital (Austin Health), the Royal Melbourne Hospital (Royal Park Campus), and Western Health. Interested parties can also self-refer in response to advertising. Gait assessments and training are conducted at the Heidelberg Repatriation Hospital (Department of Physiotherapy) and the Victoria University (Footscray Park) Biomechanics Laboratory.

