### Randomization

Randomization to participant group will be performed by the project coordinator using a secure, web-based Research Electronic Data Capture (REDCap) tool hosted at Victoria University [26]. The participant group allocation will then be e-mailed to the intervention therapist with the subject heading Randomization of (Participant ID). Participants will be coded and only available to authorized project personnel.

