### Data management and statistical analysis

All data will be stored via REDCap, an application specifically designed for the safe storage of clinical research data, for seven years. Only research personnel associated with the study will have access to the data and it will not be available to external agencies. Optotrak, IMU, and Pedar data will be coded so no personal information will be identified in the data. De-identified data will also be stored on a secure drive at the University. The patient’s gait kinematics are monitored as the project progresses to confirm no adverse effects of gait training, such as increased tripping risk. External auditing is not required in this study because all experimenters are trained to identify and record adverse events.

MTC data obtained from the treadmill walking will be analyzed using two intervention group comparisons and repeated measures ANOVA of the intervention groups and change scores, with post-hoc comparisons where relevant. Walking speed will be used as a co-variate due to its influence on MTC data. The between-subject factor will be treatment group (No-feedback and Feedback) with Time (pre-training baseline, post-training, one month, three months, and six months) being the within-subject factor.Between-group comparisons of MTC post-training will reveal effectiveness of the biofeedback gait training method in improving MTC.The within-subject analysis of the Feedback group will reveal the biofeedback effects on MTC by comparing each participant’s after intervention (post-training) data to that obtained in retention conditions, i.e. MTC data at one month (short-term retention) and at three months and six months (long-term retention).MTC data collected during overground walking during retention conditions will determine whether any changes in MTC are translated to overground walking.

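### Two laboratories train and assess participants, but the stated MTC model has no laboratory term; adding one is a small, nearly free gain in precision

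*Protocol article*

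**What the plan says.** Under the heading on recruitment and study settings, the article places both training and outcome measurement at two facilities: "Gait assessments and training are conducted at the Heidelberg Repatriation Hospital (Department of Physiotherapy) and the Victoria University (Footscray Park) Biomechanics Laboratory".

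The section on data management and statistical analysis sets out the treadmill MTC model:

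- Factors: "The between-subject factor will be treatment group (No-feedback and Feedback) with Time", where time has five levels from pre-training baseline to six months.
- Covariate: "Walking speed will be used as a co-variate due to its influence on MTC data".
- Form of analysis: "repeated measures ANOVA of the intervention groups and change scores, with post-hoc comparisons where relevant".
- Where effectiveness is read: "Between-group comparisons of MTC post-training will reveal effectiveness of the biofeedback gait training method in improving MTC".

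Laboratory appears neither as a factor nor as a covariate. The design statement gives the allocation as 1:1. The randomization section says "Randomization to participant group will be performed by the project coordinator using a secure, web-based Research Electronic Data Capture (REDCap) tool hosted at Victoria University" and names no stratification factor. The article does not say whether a participant attends the same laboratory for every assessment.

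**The concern.** One facility is a hospital physiotherapy department and the other a university biomechanics laboratory. They could differ in set-up, staff or the kind of participant who attends, and so in mean MTC. The authors already adjust for one nuisance influence on MTC, walking speed, and give a reason for doing so. They do not adjust for a grouping that their own design creates.

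If the laboratories do differ, the difference becomes unexplained between-participant variation in any comparison of MTC levels. A chance difference between arms in laboratory mix also moves the estimate in an individual trial. What is at stake is precision and some power.

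**Working it through.** **Inputs from the sample size section.** Effect size f = 0.25; 2 × 2 repeated measures design (m = 2 time points); α = 0.05; power 0.85; correlation ρ = 0.7; 126 participants (63 per group) before drop-out; SD of MTC 0.77 cm; mean MTC 1.4 cm.

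**Assumptions, not in the documents.** A constant laboratory offset of d within-laboratory SDs; a share p = 0.5 of participants at each laboratory; allocation not stratified by laboratory; each participant in one laboratory throughout.

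**Step 1: reproduce the plan's figure.** For the between-group effect, the noncentrality is λ = N·m·f² / (1 + (m − 1)ρ). At N = 126, λ = 126 × 2 × 0.0625 / 1.7 = 9.26 on 1 and 124 degrees of freedom, and power is 0.855. At N = 124 power is 0.8498, so 126 is the smallest even N that reaches 0.85. The group-by-time version, λ = N·m·f² / (1 − ρ), would need only 24. The stated 126 therefore belongs to the between-group effect, which is the group difference averaged over the two time points.

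**Step 2: effect of leaving laboratory out.** In SD² units, the variance of a participant's two-time mean is (1 + 0.7)/2 = 0.85. An omitted laboratory offset adds p(1 − p)d² = 0.25d², so λ is divided by 1 + 0.25d²/0.85. For a single post-training value, the error variance is multiplied by 1 + 0.25d².

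| Offset d (SD) | cm (× 0.77) | Variance ratio, two-time mean | Power at 126 | N for 0.85 | Variance ratio, post-training |
|---|---|---|---|---|---|
| 0 | 0 | 1.000 | 0.855 | 126 | 1.000 |
| 0.2 | 0.15 | 1.012 | 0.851 | 126 | 1.010 |
| 0.3 | 0.23 | 1.026 | 0.846 | 128 | 1.022 |
| 0.5 | 0.39 | 1.074 | 0.830 | 134 | 1.062 |
| 0.8 | 0.62 | 1.188 | 0.791 | 148 | 1.160 |
| 1.0 | 0.77 | 1.294 | 0.756 | 160 | 1.250 |

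With laboratory in the model, power at 126 returns to about 0.855 for one degree of freedom. With a 30:70 split in place of 50:50 the losses are slightly smaller: power is 0.834 at d = 0.5 and 0.772 at d = 1.0.

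**Step 3: chance imbalance.** With 63 per arm, the SD of the arm difference in laboratory share is √(0.25 × 2/63) = 0.089, and its 95% limit is 1.96 × 0.089 = ±0.175. The raw post-training difference could therefore shift by up to 0.175d: 0.087 SD (0.07 cm) at d = 0.5 and 0.175 SD (0.13 cm) at d = 1.0. This shift averages to zero over randomizations. It is the same variance as in Step 2, seen within one trial.

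**Step 4: simulation.** Settings: 63 per arm, correlation 0.7, 3,000 runs, true post-training effect 0.5 SD.

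| Power | d = 0 | d = 0.5 | d = 1.0 |
|---|---|---|---|
| Post-training, laboratory omitted | 0.784 | 0.761 | 0.711 |
| Post-training, laboratory included | 0.780 | 0.787 | 0.797 |
| Change score, laboratory omitted | 0.949 | 0.952 | 0.947 |

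With no true effect, rejection rates lay between 0.040 and 0.053 across all settings and models. Change-score power does not move, as expected, because a constant offset subtracts out.

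**The case against.** The strongest reply is that the planned analysis largely deals with this already. Baseline is a level of the time factor and change scores are named, so a constant offset drops out of both. The sentence that reads effectiveness from post-training MTC sits beneath that model and need not mean a raw comparison of levels. This stands for change scores and the group-by-time contrast, provided that participants stay in one laboratory, which the article does not say. It does not cover the between-group effect that the 126 was calculated for, or a post-training comparison taken at face value.

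Second, no laboratory difference is documented. The article names one motion-capture system and one marker procedure, and it keeps walking speed and shoes the same for each participant. The walking-speed covariate may absorb part of any difference in who attends where. An offset of 1 SD would be 0.77/1.4 = 55% of mean MTC, which is hard to credit for two rooms using the same named system. The 0.77 cm SD may also already contain laboratory variation. In that case the planned power already allows for it, and adjustment would add power above the plan. All of this stands and keeps the point small.

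Third, this is a condensed article, and an analysis plan that is not shown might include laboratory. That is possible. However, the article states the between-subject factor and the covariate outright, so the comment is on a stated model. If laboratory is already in the full plan, confirming it closes the point.

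A reader might also infer that omitting laboratory biases the treatment effect or undermines the test. The documents do not support that. Under 1:1 randomization, imbalance in laboratory mix is a matter of chance. It costs precision, and the rejection rate under no effect stays near 0.05.

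**Conclusion.** The point holds as a minor one. Two facilities train and assess participants, and the stated MTC model ignores which one was used. If the laboratories differ in mean MTC, the between-group effect that sized the trial and the post-training comparison both lose precision. Under an even split, the power loss at 126 is about one percentage point or less for offsets up to 0.3 SD, about 2.5 points at 0.5 SD and about 10 points at 1 SD. The documents give no offset, so these figures show a range and do not predict a loss.

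It would go too far to say that the laboratories do differ, that the trial is underpowered, or that the missing mention of stratification is a fault. The article supports none of these. A constant offset leaves change scores and the group-by-time contrast untouched for participants who stay in one laboratory. What could remain there is a laboratory difference in change over time, or the effect of switching laboratory, and the article gives no figure for either.

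**What to change.** Add the laboratory of the baseline assessment as a fixed between-subject factor in the treadmill MTC model and in any overground MTC comparison, and specify this before unblinding. In the repeated-measures model, include laboratory-by-time as well, so that a laboratory difference in change over time is also removed. State whether each participant is assessed in the same laboratory at every visit, because the cancellation in change scores depends on it.

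The cost is a line of analysis text, one between-subject degree of freedom, and (2 − 1) × (5 − 1) = 4 within-subject degrees of freedom for the interaction over the five time points. The laboratory should be available from the assessment records, and randomization need not change. If there is no offset, almost nothing is lost: simulated post-training power was 0.784 without the term and 0.780 with it.

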### Randomization

Randomization to participant group will be performed by the project coordinator using a secure, web-based Research Electronic Data Capture (REDCap) tool hosted at Victoria University [26]. The participant group allocation will then be e-mailed to the intervention therapist with the subject heading Randomization of (Participant ID). Participants will be coded and only available to authorized project personnel.

### Blinding

Clinical physiotherapists will be involved in assessment but blinded to group allocation and training sessions. Blinded clinical physiotherapists will conduct clinical assessments and collect falls-related data. Biomechanical gait assessors who conduct the movement analysis are, similarly, blinded to group allocation to ensure that all assessment personnel are blinded as to the participant’s group assignment. Physiotherapists and biomechanists delivering the gait training are required to know the patient’s group assignment.

### Intervention

All participants, both controls and those in the feedback intervention group, will walk on the treadmill following an identical schedule of training sessions. Self-selected walking speed will be determined following treadmill familiarization with a physiotherapist during the first clinical assessment visit. This self-selected walking speed will be recorded and each treadmill walking session will be conducted at the same walking speed. All participants wear a safety harness when treadmill walking and continue for up to 10 min with rest breaks as required. Previous research by the authors had determined 10 min to be comfortable maximum for this population. Participants will wear the same comfortable shoes for all walking activities.

Participants randomized to the intervention group undertake biofeedback gait-training using a real-time display of the affected limb’s swing phase trajectory, with toe clearance and the associated MTC event clearly shown. Motion analysis markers will be attached to the shoe and other body segments to calculate toe clearance parameters in real-time as per the established protocol [6]. *Target* MTC will be calculated as baseline MTC plus 1 SD. The feedback group will be asked to move their affected limb such that MTC falls between target MTC mean + 0.5SD and target MTC-0.5SD, projected as parallel lines on a screen in front of the treadmill [16, 17]. If baseline MTC cannot be calculated, target boundaries will be set using the *maximum* toe clearance (TC) with instructions to control foot motion within that target band. Borg Ratings of Perceived Exertion will be recorded after each session.

Biofeedback is presented for the first six sessions then progressively reduced (faded) across the remaining four sessions. During fading, one-third of the initial feedback will be available at the beginning of session 7, one-third in the middle for session 8, one-third at the end of session 9, and, finally, one-10th at the beginning and one-10th at the end of session 10. As indicated above, the control group will walk under the same conditions without either feedback or any instructions concerning their gait control. Adherence to the gait training program will be reflected in the number of training sessions successfully completed and the research team will monitor any non-adherence.

### Outcome measures

#### Assessments

A clinical assessment is conducted on the first visit (baseline) in order to describe the study population. Clinical assessments for global function, lower limb strength, gait speed, and falls risk are repeated following the final training session and at one, three, and six months after training. Clinical measures undertaken by the research physiotherapists will include:Functional Independence Measure (FIM) [18], a measure of global function;Timed Chair Stand Test [20], an indicator of lower limb strength;Timed 10-m Walk Test [19], an assessment of gait speed;Step Test [21], a balance measure that identifies stroke patients with a risk of falls;Sensory Testing (light touch, pinprick, and sensory extinction);Star cancellation test; to screen for visual-spatial neglect [27];Stroke Rehabilitation Assessment of Movement (STREAM) [22], measures voluntary movement and mobility in people with stroke;Tardieu scale [23], to assess spasticity in gastrocnemius and soleus;Six-minute walk test [24], a measure of walking endurance;Falls Risk for Older People in the Community (FROP-Com). The FROP-Com has previously been used to identify falls risk in people with stroke [10].

Gait assessment trials are conducted at baseline, after the final training session (a minimum of 20 min following final training) and one, three, and six months later. These gait data are collected during treadmill and overground walking by biomechanics personnel blinded to group allocation. During overground walking assessments (before and after training) participants walk at preferred speed along an 8-m walkway. Kinematic (position/time) data are captured using a three-dimensional motion analysis system (Optotrak®, NDI, Canada) with clusters of infrared markers fixed to the toe of the shoe and the shank, thigh, and pelvis segments. Bony landmarks on the foot, ankle, knee, and hip are identified using virtual markers and used with the clusters in order to construct a model of the joints and segments. This enables kinematic data, including joint angles, to be calculated. Foot plantar pressures and center of pressure excursion (COPE) are captured to assess gait stability using the Pedar foot pressure insole (Novel, Germany), an in-shoe system that measures plantar pressure distribution within the shoe.

